### Measurements

The following primary parameters were used to determine the effect of the study medication

#### Muscle strength and muscle power

Maximum voluntary isometric knee extension strength (both legs) was measured as the force applied at the ankle, with the subject seated in an adjustable straight-back chair, the lower leg unsupported and the knee flexed to 90°. Force was measured with a strain gauge and recorded with a strain meter [18,19].

Explosive leg extensor power (both legs) was assessed with the Nottingham Power Rig. The subject, in a seated position with folded arms, gave a maximal push to a large foot pedal setting a flywheel in motion. The initial flywheel speed reflects the leg extensor power of the subject [20]. The measurement was repeated for at least five efforts, until no further improvements were seen.

Handgrip strength (both hands), which is associated with general muscle strength, was measured with a handgrip mechanical dynamometer [21]. The best of at least three attempts for each hand was recorded.

#### Bone mineral density (BMD)

BMD, measured by DEXA, was measured at the lumbar vertebrae (L1–L4, calculated from the total bone mineral content and the total area of the four lumbar vertebrae) and at the hip (neck, trochanter, and intertrochanteric region). DEXA scanner precision was carefully registered by means of a dedicated Hologic spine phantom. DEXA measurements were conducted at the Julius Center for Health Sciences and Primary Care, University Medical Center Utrecht, the Netherlands.

The following secondary parameters were used to determine the effect of the study medication:

#### Functional mobility, balance, endurance and body composition

Functional mobility was assessed quantitatively with the timed "get up & go" test [22]. The subject performed the test three times as fast as possible and the fastest time (recorded in seconds) was used for analysis.

Postural balance was assessed by means of an analysis of body sway and by the functional reach test. Body sway was assessed with both eyes open and both eyes closed [23]. In the Functional Reach the maximal push is recorded in cm [24].

Endurance was measured with the 6-minute walking test. (modified Cooper test) [25]. Body composition was measured by bio-electrical impedance analysis (BIA) and by DEXA. DEXA measurements were only performed at baseline and 24 months. The principle of BIA is that lean tissues, which mainly consist of electrolyte-containing water, readily conduct an applied current, whereas fat does not or only minimally. A current of 800 μA at a signal frequency of 50 Hz was generated by a bioelectrical impedance analyzer and was applied to the subject through electrodes that were placed on the wrist and the ankle on one side of the body [26]. Total body fat distribution and four sub-regions of leg fat distribution were determined from the DEXA scans [27,28].

#### Quality of life, well-being and mood/depression

Quality of life was measured with the Women's Health Questionnaire (WHQ) and the EQ-5D questionnaire [29,30]. The EuroQol (EQ-5D) questionnaire was developed by a European group as a standard non-disease-specific instrument for describing and valuing quality of life (EuroQol, Kind). It is a descriptive classification system consisting of five items, each with three levels. [31-33]

Mood/depression was measured with the Geriatric Depression Scale (GDS). This test is designed to assess for depression in older adults, independent of somatic symptoms [34,35]. It can also be used as indicator of severity of psychopathology.

Anxiety was measured with the Dutch Version of the State-Trait Anxiety Inventory (Self-Judgment Questionnaire = STAI-DY). The STAI was specifically designed to be self-administered. The test has a uniformly high level of internal consistency [36,37].

#### Cognitive function (15 Words test; Trails B test)

Cognitive function was assessed with the Groningen 15 Words test [38,39] and the Trails B test. The Groningen 15 Words test is an improved version of a test originally devised by Rey [40]. Briefly, 15 words are presented, one after another. Then the subject is asked to recall as many words as she can. This procedure is repeated 5 times, so that a learning curve can be plotted. The total number of words and the maximum number of words recalled over five trials are taken as dependent measures of learning and short-term memory. After a delay of 20 minutes (during which another test is administered), a recall trial is carried out without presentation of the list. The score at this delayed recall comprises the long-term memory score. The Trails B test measures speeded mental operations, attention, visual scanning, visual sequential abilities, and mental flexibility. The test is sensitive to aging effects [41,42].

### Compliance monitoring

Compliance with treatment was checked by means of a diary card and by counting the remaining tablets at each visit. Subjects who missed more than 6 days of trial medication in 4 weeks were excluded.

### Adverse event/Serious adverse event

The investigator decided whether an abnormal laboratory/vital sign was clinically relevant and should be entered on the adverse event form. If the AE met the definition of a serious adverse event (SAE), the procedure for SAEs was followed.

Serious adverse event was defined as any untoward medical occurrence that at any dose results in death, is life-threatening, requires in-patient hospitalization or prolongation of existing hospitalization, or results in persistent or significant disability/incapacity. It should be noted the term 'life-threatening' refers to an event in which the patient was at risk of death at the time of the event; it does not refer to an event that hypothetically might have caused death if it had been more severe.

Medical and scientific judgment was exercised in deciding whether major medical events that were not be immediately 'life-threatening' or result in death or hospitalization but which might jeopardize the patient or might require intervention to prevent one of the other outcomes listed in the definition above should be considered serious. All SAE's were reported to the Institutional Review Board of the University Medical Center of Utrecht, Utrecht, the Netherlands, to Organon NV, Oss the Netherlands and to Lilly Nederland B.V, Houten, the Netherlands.

### Power calculation

Changes in muscle strength and BMD are the primary endpoints to judge the efficacy of supplementation with both study drugs. In order to demonstrate a between-group difference in handgrip strength of at least 3.6% and a difference in BMD of at least 2.6%, a power calculation indicated 75 subjects per group completing the study. To allow for drop-out and protocol violations, it was calculated that 324 subjects would need to be recruited, 108 in each intervention arm. This number is based on conventional assumptions of alpha = 0.05 and beta = 0.2 and a drop-out of 30%. Mean and SD for handgrip strength were taken from our previous study on the effect of tibolone in postmenopausal women [13].

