**Methods:**

We recruited 318 elderly women in our single-center randomized, double-blind, double-dummy, placebo-controlled trial. Participants were randomized to tibolone 1.25 mg (Org OD 14, Organon NV, the Netherlands) plus placebo, raloxifene 60 mg (Evista^®^, Eli Lilly, United States) plus placebo or two placebo tablets daily for 24 months.

The primary aim is to determine if there is a difference between tibolone and placebo or if there is a difference between raloxifene and placebo. Primary endpoints are muscle strength and bone mineral density. The secondary endpoints are postural balance, body composition, cognitive function, anxiety, mood and quality of life. The secondary aim is to determine if there is a difference between tibolone and raloxifene.

The measure of effect is the change from the baseline visit to the visits after 3 months, 6 months, 12 months, and 24 months. A follow-up measurement is planned at 30 months to determine whether any effects are sustained after cessation of the study. By December 2007 the blind will be broken and the data analyzed.

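### Three strength measures and four BMD sites are all primary, for either of two drugs, with one alpha of 0.05 and no ranking, alpha split or both-must-succeed rule

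*Protocol article*

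**What the plan says.** All references are to the protocol article.

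- **Aim (Abstract, Methods).** The trial is to determine "if there is a difference between tibolone and placebo or if there is a difference between raloxifene and placebo". The same paragraph states: "Primary endpoints are muscle strength and bone mineral density".
- **Measure of effect (Abstract, Methods).** It is the "change from the baseline visit to the visits after 3 months, 6 months, 12 months, and 24 months". No visit is named as primary. Table 4 shows muscle strength at all four of these visits, but BMD only at baseline and month 24.
- **What is primary (Measurements).** The list opens with "The following primary parameters were used to determine the effect of the study medication". Before the secondary parameters begin, it covers isometric knee extension, leg extensor power and handgrip, each measured on both sides. It also covers BMD at the lumbar spine and "at the hip (neck, trochanter, and intertrochanteric region".
- **Sample size (Power calculation).** The section opens: "Changes in muscle strength and BMD are the primary endpoints to judge the efficacy of supplementation with both study drugs". The plan needs 75 completers per group, for a handgrip difference of 3.6% and a BMD difference of 2.6%. It adds: "This number is based on conventional assumptions of alpha = 0.05 and beta = 0.2 and a drop-out of 30" per cent.
- **Analysis (Efficacy parameters).** Each parameter has its own covariance model, reported with a 95% confidence interval and a two-sided P-value. No adjustment is mentioned.
- **Tibolone (Efficacy).** After the arm was stopped, its analyses use the 3-, 6- and 12-month data, with 44 women at 12 months. The only sequential rule opens the tibolone-raloxifene comparison if both drugs show a significant benefit.

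**The concern.** The text fixes a family of primary results but not how a primary claim is reached from it. A reader cannot tell whether a benefit on muscle strength means handgrip, knee extension, leg power or any of them, or at which visit. The same holds for BMD and its four sites. Someone who sees the results could report whichever parameter crosses 0.05 as the primary finding, while the error rate behind the sample size is that of a single unadjusted comparison.

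The plan's own gate to the tibolone-raloxifene comparison has the same weakness. It depends on both drugs being significant, yet no measure, site or visit is named on which to judge that.

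**Working it through.** **1. The plan's own figure.** 75 / (1 - 0.30) = 107.1, rounded up to 108 per arm, and 3 × 108 = 324. This matches the Power calculation section.

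No SD is printed, so the 75 cannot be rebuilt directly. Working backwards for one two-group test at two-sided 0.05 and 80% power:

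- d = (1.960 + 0.842) × √(2/75) = 0.457.
- Implied SD for handgrip: 3.6% / 0.457 = 7.9%.
- Implied SD for BMD: 2.6% / 0.457 = 5.7%.

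The 75 is therefore what one unadjusted test per endpoint would need if the SDs are of that size.

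**2. Counting the tests the current plan contains.**

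- Raloxifene, one measure per endpoint: 2.
- The same plus tibolone strength: 3. Tibolone BMD is left out because its analyses end at 12 months and BMD is scheduled at month 24.
- Raloxifene at month 24, as listed: 3 strength + 4 BMD = 7.
- Raloxifene with strength at all visits: 3 × 4 + 4 = 16.

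**3. Chance of at least one false positive.** All null hypotheses are true and each test is two-sided at 0.05. Under independence the chance is 1 - 0.95^m. The last column comes from simulating correlated normal test statistics.

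| Tests | Independent | Correlated |
|---|---|---|
| 2 | 1 - 0.95² = 9.75% | 9-10% |
| 3 | 1 - 0.95³ = 14.3% | 13-14% |
| 7 | 1 - 0.95⁷ = 30.2% | about 20-28% |
| 16 | 1 - 0.95¹⁶ = 56.0% | about 27-49% |

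The documents give no correlations, so these are assumptions. For 7 and 16 tests, the within-endpoint correlation runs from 0.8 (lower figure) to 0.3 (upper figure), with 0.2 between endpoints. In the three-test case the drugs share the placebo arm, which gives a correlation of 0.5 with equal arms. Left and right sides are not counted separately.

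**4. The reading that would remove the problem.** If a drug had to succeed on both endpoints, with one test each, the chance of a false claim for either drug is 0.5-0.9% under the global null (endpoint correlation 0 to 0.3). It is at most about 9% if both drugs truly affect one endpoint.

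**5. Power after a split.** With 75 per arm, d√(75/2) = 2.802.

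- At 0.05: Φ(2.802 - 1.960) = 80%.
- At 0.025: Φ(2.802 - 2.241) = 71%.

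**The case against.** The strongest reply is that the inflation depends on a decision rule the article does not state. Alpha = 0.05 appears only as a sample-size assumption, and the analysis section promises estimates, intervals and P-values without saying that any one significant result wins. The *or* in the aim joins the drugs, not the endpoints, and the Power calculation joins handgrip and BMD with *and*. A both-must-succeed reading would remove most of the inflation. An analysis plan, not shown, may also hold an adjustment.

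Part of this stands: per-test use of 0.05 is inferred, and the sizes above are conditional on it. But the *and* describes the differences the trial should detect and is not a success rule. Which outcomes are primary, and the alpha behind the sample size, are fixed in this text, and it makes seven parameters primary without ranking them.

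It can also be argued that separate drugs need no joint adjustment. Raloxifene alone still gives 9-10% or more.

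A reader might infer more than the documents support:

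- **That only handgrip sized the trial.** The Power calculation also names a 2.6% BMD difference. Handgrip is only the measure whose SD source is given.
- **That both endpoints are multiplied by visits.** BMD has one post-baseline visit in Table 4.
- **That the family is two drugs by two endpoints, at about 17%.** That was the design before tibolone was stopped. Three tests, at 13-14%, is the fairer count.
- **That left and right limbs are tested separately.** The article says both sides were measured, not that each is tested.

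**Conclusion.** The concern holds in this form: as written, the plan does not limit a false primary claim to 5%. If any significant primary parameter counts, the rate is about twice 0.05 on the mildest count (raloxifene, one test per endpoint). It is four to nearly six times 0.05 for raloxifene's month-24 parameters as listed (20% / 5% = 4; 28% / 5% = 5.6), and more with every strength visit. The exact sizes depend on the assumed correlations and on all nulls being true. Of the readings considered, only a both-must-succeed rule on single named tests would remove most of the inflation, and the text does not contain one. The documents do not support saying that the plan declares 0.05 for every test; they support saying that nothing in it prevents this.

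**What to change.** Name two primary tests, both for raloxifene versus placebo at month 24:

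1. Handgrip strength, the strength measure used in the sample size, reduced to one value per woman by a stated rule.
2. BMD at one named site.

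Then state one decision rule: either Holm at overall two-sided 0.05, or success only if both are significant. Label the other strength measures, the other BMD sites, the earlier visits and the truncated tibolone comparison as secondary or exploratory, reported with intervals and without a primary claim. State which result opens the tibolone-raloxifene comparison.

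The Abstract has the blind broken by December 2007. If that has happened, the report must say that these choices were made after unblinding.

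The change is to wording and needs no new data. Its cost is lower stated power. With 75 per arm, each endpoint has about 71% rather than 80% at the 0.025 Holm step. Restoring 80% there would take 2 × (2.241 + 0.842)² / 0.457² ≈ 91 completers per group. If both must succeed, joint power is about 0.80 × 0.80 = 64% when the endpoints are independent and each has 80%, and somewhat higher if they are positively correlated.

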### Data analysis

#### Efficacy

Analysis will be done concerning tibolone versus placebo and raloxifene versus placebo. If both show a significant beneficial effect, the difference between tibolone and raloxifene will be analysed. However, this is not expected. After termination of the Tibolone-arm during our study, our concern is that the tibolone-placebo comparison will be underpowered. Analyses will be done with 3 months, 6 months en 12 months (n = 44) data to determine whether there is a treatment effect of tibolone. In previous studies with a comparable number of participants or fewer, a significant beneficial effect was reported on body composition after 1 year of treatment [43,44], so we might find an effect as well.

The efficacy analysis will be based on the intention to treat group (ITT), all subjects of the treated group who had at least one post baseline assessment of at least one of the primary outcome variables. In addition a per-protocol (PP) analysis will be performed, using data for all subjects from ITT group without any major protocol violation. Differences between the ITT and PP results will be examined.

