#### Efficacy parameters

For all parameters, descriptive statistics will be calculated by treatment group and assessment. In addition, the change from baseline values will be calculated. If a Gaussian distribution can be assumed, each parameter will be analyzed by means of a multiple analysis of covariance model. This model will incorporate treatment group as a factor and the baseline value as a covariant. Scatter plots will be used to assess the adequacy of the analysis of covariance and to detect outliers. Results will be expressed as estimates of the treatment differences with 95%-confidence intervals and two-sided P-values.

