## Conclusion

This trial will analyse the differences in effect of tibolone and raloxifene on several endpoints. To the best of our knowledge this randomized controlled double-blind, placebo-controlled trial is the first to assess the main effect of tibolone and raloxifene on muscle strength and functional mobility next to bone mineral density in a female population older than 70 years of age. Research has never been conducted on the effect of raloxifene on muscle strength and functional mobility.

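### The tibolone–raloxifene difference is an unconditional secondary aim, but it is analysed only if both drugs beat placebo, so it goes unanswered when one drug works and the other does not

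*Protocol article*

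**What the plan says.** The Methods part of the abstract makes each drug's comparison with placebo primary and then adds: "The secondary aim is to determine if there is a difference between tibolone and raloxifene". No condition is attached.

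The Efficacy section under Data analysis starts with the primary comparisons: "Analysis will be done concerning tibolone versus placebo and raloxifene versus placebo". It then makes the drug-to-drug comparison depend on their results: "If both show a significant beneficial effect, the difference between tibolone and raloxifene will be analysed. However, this is not expected". The same paragraph expresses concern that tibolone against placebo will lack power now that the arm has been stopped. It limits the tibolone analyses to the 3, 6 and 12 month data, with 44 women.

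The Efficacy parameters section describes an analysis of covariance with treatment group as a factor and baseline as a covariate, reporting "estimates of the treatment differences with 95%-confidence intervals and two-sided P-values". It does not mention the condition, either to repeat it or to remove it. The Conclusion says in general terms: "This trial will analyse the differences in effect of tibolone and raloxifene on several endpoints".

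**The concern.** An aim stated without a condition is tied to a rule that can prevent any analysis of it. The rule looks at two placebo comparisons, and neither of them tests the difference between the drugs. If one drug improves strength and the other does nothing, the drugs differ. The inactive drug will nearly always fail against placebo, so the direct contrast is not analysed. The report would then hold one significant and one non-significant placebo comparison, and setting these side by side is not a test of their difference.

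The early stop of the tibolone arm adds to this. A tibolone effect of the planned size may miss significance because only 44 women have one-year data, and that alone would block the comparison with raloxifene.

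**Working it through.** **The plan's own figure.** The Power calculation section states that "a power calculation indicated 75 subjects per group completing the study", and: "This number is based on conventional assumptions of alpha = 0.05 and beta = 0.2 and a drop-out of 30" per cent. 75 / (1 − 0.30) = 107.1, rounded up to 108 per arm, and 3 × 108 = 324. This agrees with the stated target.

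**Effect size (assumption).** The section gives a "between-group difference in handgrip strength of at least 3.6% and a difference in BMD of at least 2.6" per cent but no SD, so the standardised effect has to be back-solved. For two means, n per group = 2(1.960 + 0.842)² / d². With n = 75, d = 2.802 × √(2/75) = 0.4575. A t-distribution in place of the normal gives 0.4605. I use d = 0.46. Using 0.4575 instead lowers each percentage below by less than one point.

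**Arm sizes.** Tibolone at 12 months is 44, as stated (105 − 15 − 27 − 19 = 44). The other arms' numbers at 12 months are not given, so I assume a range:
- Upper value: 75, the planned completers.
- Lower value: 67. Outside tibolone, 318 − 105 = 213 were randomised and 35 − 15 = 20 never started. That leaves 193, or 96.5 per arm, and 96.5 × 0.70 = 67.6.

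**Direct contrast, one drug at d and the other at zero.** SE (in SD units) = √(1/n_T + 1/n_R), and power = Φ(d/SE − 1.960).
- 44 against 67: SE = 0.1940, d/SE = 2.371, power = Φ(0.411) = 66%.
- 44 against 75: SE = 0.1899, d/SE = 2.422, power = Φ(0.462) = 68%.

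**Probability that the condition is met.** Both placebo comparisons must be significant at two-sided 0.05 in the beneficial direction. The two test statistics share the placebo arm, so they are bivariate normal with correlation (1/n_P) / (SE_TP × SE_RP). This is 0.445 for 44/67/67 and 0.430 for 44/75/75.

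| True effects (tibolone, raloxifene) | Met, 44/67/67 | Met, 44/75/75 | Direct contrast significant |
|---|---|---|---|
| d, 0 | 2.4% | 2.4% | 66%, 68% |
| 0, d | 2.4% | 2.4% | 66%, 68% |
| d, d (no difference) | 56% | 59% | 5% |
| d, d/2 | 23% | 25% | 22%, 23% |
| 2d, d | 76% | 80% | 66%, 68% |
| d, 2d | 66% | 68% | 66%, 68% |

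In the first two rows, the share of trials in which the contrast is both analysed and significant is below 1%. With the planned 75 in every arm and one active drug, the condition is met in 2.5% of trials and the direct contrast is significant in 80%.

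**A bound that needs neither d nor the arm sizes.** If one drug has no effect, the condition requires that drug to be significantly better than placebo by chance. On a single endpoint that has probability 0.025, so the condition cannot be met in more than 2.5% of such trials.

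**The case against.** The strongest defence is that this is an ordinary hierarchy. The placebo comparisons are primary, drug against drug is secondary, and testing the secondary only after both primaries succeed protects the error rate. Comparing two drugs is also of most interest when both work. This would justify withholding a significance claim. It does not justify withholding the estimate and its interval, and the article gives no multiplicity reason for the rule.

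Four other points limit the concern.

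- A reader might infer that the aim is lost whenever the drugs differ. That is not so. If both beat placebo by different amounts, the condition is often met: 66 to 80% of trials when one drug has twice the other's effect.
- A reader might infer that the authors predict their own condition will fail. The second sentence of "If both show a significant beneficial effect, the difference between tibolone and raloxifene will be analysed. However, this is not expected" may mean that, or that no difference between the drugs is expected. The condition stands on either reading.
- A reader might infer that the authors intend to read a drug difference from one significant and one non-significant result. Nothing in the article says so. The risk is only left open.
- The sentence in the Conclusion is a loose summary and sets no analysis rule, so the case does not rest on it. The Efficacy parameters section does not restrict its estimates to placebo contrasts, but it does not lift the explicit condition either.

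The figures also assume that the condition is judged endpoint by endpoint. The article does not say on which endpoint both drugs must succeed. If success on any of several endpoints counted, the condition would be met more often.

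**Conclusion.** The point holds as an inconsistency between the unconditional aim in the abstract and the conditional rule in the Efficacy section. Its practical effect is on the case where one drug works and the other does not. There the comparison is made in about 2.4% of trials, and in at most 2.5% on a single endpoint, while the direct contrast would be significant in about 66 to 68%. With both drugs at the design effect it is made in about 56 to 59%, where there is no difference to find.

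The 2.5% bound does not depend on the assumed inputs. The other percentages rest on an effect of about 0.46 SD, 44 tibolone women and an assumed 67 to 75 in each other arm. The documents do not support the broader statement that the aim fails whenever the drugs differ. The consequence is confined to a secondary aim, and the primary comparisons are unaffected. It should be corrected, but it does not threaten the trial's main analysis.

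**What to change.** In the Efficacy section, replace the condition with wording such as: *The tibolone minus raloxifene difference will be estimated with a 95% confidence interval from the same analysis of covariance at 3, 6 and 12 months, whatever the placebo comparisons show, as a secondary estimate without an alpha claim. No difference between the drugs will be inferred from one significant and one non-significant placebo comparison.*

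State also that this covers only endpoints measured at those visits. Muscle strength is included. BMD is not, because Table 4 schedules it only at baseline and 24 months.

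The abstract planned unblinding by December 2007 and the article is dated June 2008. If the change is made after unblinding, label it post hoc.

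The cost is a few sentences and one more contrast from a model already planned, with no further data. Restating the aim as conditional would remove the contradiction, but the case of one active drug would still go unanswered.
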